### 3.5 Questionnaires

Data collection tools will target both family-level and individual-level outcomes. The family unit will be assessed for food security and socioeconomic factors, while individual-level data will be gathered for specific health and nutritional outcomes. For example, the *Household Food Insecurity Access Scale (HFIAS)* is designed to capture food security at the household level, while the *Short Form-36 Health Survey (SF-36)* and the *World Health Organization Quality of Life (WHOQOL-100)* questionnaire are individually administered to adult members to evaluate personal health and quality of life. Additionally, the *Pediatric Quality of Life Inventory (PedsQL)* will be used for children's health-related quality of life, completed by their caregivers.

#### 3.5.1 Nutritional situation

Nutritional status will be assessed using the *Mini Nutritional Assessment* (*MNA*) (38). The MNA is a comprehensive tool designed to evaluate nutritional status. It encompasses a series of questions and assessments that collectively provide insights into an individual's dietary habits, health status, and overall risk of malnutrition. This study will incorporate 14 specific questions from the MNA, covering various dimensions such as dietary diversity, protein intake, fruit and vegetable consumption, and any recent changes in food intake due to loss of appetite, digestive problems, or chewing issues.

Given that the *Mini Nutritional Assessment (MNA)* is intended for evaluating the risk of undernutrition specifically in older adults, this tool will be used only with older adult participants in our sample. For other age groups, nutritional status will be assessed using anthropometric measurements, including weight, height, and age, to calculate Body Mass Index (BMI) and other relevant indicators. Additionally, dietary diversity at the family level will be evaluated using a modified dietary diversity questionnaire, which is more applicable to all age groups and provides insights into household dietary patterns.

#### 3.5.2 Socioeconomic situation

The assessment of the socioeconomic situation within this study will be conducted using an adapted version of the Socioeconomic Level Stratification Survey questionnaire, originally implemented by the Instituto Nacional de Estadística y Censos (INEC) of Ecuador in 2011 (39). This comprehensive tool consists of twenty-five carefully selected questions for the Ecuadorian context designed to capture a wide range of socioeconomic indicators.

#### 3.5.3 Health situation

Health status was assessed using four questionnaires. These questionnaires were *the Short Form*-*36* Health Survey (*SF*-*36*) (40), *the Household Food Insecurity Access Scale* (*HFIAS*), *The World Health Organization Quality of Life* (*WHOQOL-100*) for adults (41), and *the Pediatric Quality of Life Inventory* (*PedsQL*) for children (42). These will include thirty-six, nine, hundred, and twenty-three questions, respectively.

To guarantee precision and contextual relevance for the Ecuadorian setting, we will employ Spanish-validated versions of all assessment tools.

#### 3.5.4 Active participation

To assess the level of engagement with the Food Forest initiative, our study will utilize a specialized self-administered questionnaire composed of five questions specifically tailored to this context. These questions are designed to explore various dimensions of participation and involvement with the Food Forest:

Frequency of interaction with the Food Forest: This question measures how often community members engage with the Food Forest, whether daily, weekly, or on a less frequent basis.Types of activities undertaken: Participants will be asked about their involvement in specific activities such as planting, harvesting, and maintenance of the forest.Contributions to planning and development: This question investigates whether participants have contributed to the planning, decision-making, or overall development of the Food Forest initiative.Collaboration with other community members: Participants will report on their interactions and collaborative efforts with other community members within the Food Forest setting.Perceived impact of participation: Finally, participants will be asked to assess how their involvement in the Food Forest has impacted both the forest and their personal or household well-being, covering both social and economic dimensions.

This questionnaire will provide valuable insights into how actively community members engage with the Food Forest and in what specific ways, helping to shed light on the initiative's integration into the community's social and economic fabric.

### 3.6 Data collection

Information will be collected in the homes of members of the communes. The data will be entered offline via tablets into Qualtrics (43).

### 3.7 Data management

Data entry for this research will be strictly managed by our team, ensuring access is limited to key researchers and statisticians who won't know participant identities. This safeguarding of data underscores our commitment to privacy and the secure use of information for analyzing the intervention's impact and authoring related papers.

### 3.8 Measurement slots

Participants will be assessed at baseline, 1 year, 3 years, and 5 years after the intervention starts. Their nutritional, socioeconomic, and health statuses will be assessed at each time point. Participants will also be asked about their active participation in the Food Forest Project.

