## Abstract

Malnutrition is an escalating concern in low-and-middle-income countries (LMICs), including Ecuador, particularly within rural settings. To address this issue, food forests emerge as a promising intervention. This research protocol outlines a controlled intervention in the province of Santa Elena, aiming to evaluate the efficacy of a food forest in enhancing nutritional outcomes, with potential implications for broader replication. The study will be conducted in the Colonche Parish of Santa Elena Canton, where one commune will be randomly selected to receive the food forest intervention. In contrast, another similarly characterized commune, also randomly selected through cluster-based sampling, will serve as a control group, receiving no intervention. This randomized, comparative approach will enable a more precise assessment of the food forest's impact. Data collection will occur at three intervals: baseline, 6 months, and 12 months post-intervention. Comprehensive questionnaires will be employed to measure the food forest's influence on the communities' nutritional, economic, and health metrics, distinguishing between the intervention and control communes to elucidate the intervention's specific effects.

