### 3.9 Measurements

Primary and secondary outcome measures will be assessed in three-time points.

The primary and secondary outcomes of this study are centered around assessing the nutritional, socioeconomic, and health statuses of the participants.

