### 3.10 Statistical analysis

All statistical analyses will be performed using Stata 18.0 (44). Descriptive statistics will be calculated for both qualitative (e.g., categorical) and quantitative (e.g., continuous) data. Categorical variables, such as employment status or food security, will be summarized using frequencies and percentages, while continuous variables, such as household income or nutritional status (e.g., BMI), will be described using means and standard deviations for normally distributed data, or medians and interquartile ranges for non-normally distributed data.

For hypothesis testing, categorical variables like food security (measured as secure/insecure) and employment status (e.g., employed/unemployed) will be compared between the intervention and control groups using Chi-square tests or Fisher's exact tests, depending on sample sizes. For continuous variables, such as changes in household income or nutritional status (e.g., BMI, dietary diversity scores), Student's *t*-tests will be used if the data are normally distributed. If normality assumptions are violated, Mann-Whitney U tests will be applied instead.

To evaluate changes over time within the same group (e.g., baseline to 6 months), paired *t*-tests will be used for normally distributed continuous variables, such as income or BMI, while Wilcoxon signed-rank tests will be used for non-normally distributed variables. For categorical variables like food security status over time, McNemar's test will be applied.

Regarding regression models, linear regression will be used to assess continuous outcomes such as household income levels, nutritional status (BMI), or dietary diversity scores. Logistic regression will be applied to binary outcomes, such as food security (secure/insecure) or whether participants report improved health (yes/no). For outcomes with multiple categories, such as levels of health perception (good, fair, poor) or employment status (employed, unemployed, seeking work), multinomial logistic regression will be used.

To account for repeated measures over time (e.g., baseline, 6 months, and 12 months post-intervention), mixed-effects models (both linear and logistic) will be employed. These models will allow us to assess the effect of the intervention across different time points while controlling for intra-individual correlations. All hypothesis tests will be two-tailed, and a *p* < 0.05 will be considered statistically significant.

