### 4.2 Content of intervention

The community's role in establishing and maintaining the food forest is structured through active participation in key phases of the project. Community members are involved from the onset in activities such as site preparation, planting, and periodic maintenance. Harvests are organized so that community members can collectively decide on usage, ensuring fair distribution and communal benefit. Regular meetings will also allow the community to provide input on project development, further strengthening local engagement and commitment to long-term maintenance.

The intervention comprises two key activities (plantations and reforestation workshops), conceived and implemented by Nedetel and CECAPROF, within the territories of the Colonche Parish communes. Designed to run concurrently, these activities span in total 5 years, allowing for a synchronized approach. This strategic implementation aims to address malnutrition and enhance the average family income in Santa Elena Province, contributing to overall community wellbeing.

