#### 4.2.1 Plantations

The initial phase of the intervention involves an innovative reforestation effort, utilizing the Food Forest technique to plant 12,500 trees across 15 hectares within Colonche Parish. This diverse selection includes ancestral trees and various species that yield food or sustainable products. A strategic allocation ensures that 30% of these trees directly contribute to enhancing the commune's nutritional needs, while the remaining 70% are designated for commercial purposes, thereby supporting economic growth.

CECAPROF takes the lead in this endeavor, overseeing the meticulous treatment of seeds and the careful transplantation of saplings, with a commitment to achieving a 90% survival rate for the newly planted flora. Spanning ~9 months, this activity not only focuses on the technical aspects of reforestation but also establishes a reliable supply chain. A collection center, operated by CECAPROF, facilitates regular access to the harvest every 3 months, ensuring the community benefits directly from the bounty.

Moreover, this initiative is protected from external and internal interference, allowing the commune exclusive rights to utilize and benefit from the reforested land. The incorporation of georeferencing technology further enhances oversight, enabling precise monitoring of the reforestation area's growth and development, thereby ensuring the project's success and sustainability.

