#### 4.2.2 Reforestation workshops

Concurrently, CECAPROF will host a series of Reforestation Workshops aimed at empowering the local community with the knowledge and skills needed to nurture and sustain the newly reforested areas. These workshops will cover a comprehensive curriculum, including seed collection techniques, seed processing methods, the construction of nurseries, and the intricacies of reforestation mapping. Additionally, participants will learn about the design and planning of reforestation projects, coupled with environmental education that highlights the significance and history of native tree species. Scheduled over 10 months, these workshops are designed to foster a deep connection between the community and their environment, ensuring the long-term success and stewardship of the reforestation efforts.

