### 4.3 Potential pitfalls and unintended effects

Several potential pitfalls and unintended effects could arise during the implementation and evaluation of the Food Forest initiative. One key challenge is the variability in participant engagement. Some community members may be more actively involved in the initiative (e.g., planting, maintaining, or harvesting), while others may not fully engage, leading to differences in outcomes that may not directly reflect the intervention's effectiveness. Additionally, external factors, such as adverse weather conditions, could impact the growth of the Food Forest and, consequently, its effects on nutritional outcomes. Furthermore, there may be difficulties in retaining participants for follow-up assessments over the twelve-month study period, particularly given the rural nature of the setting, which may affect the continuity of data collection. To mitigate these risks, we will implement regular check-ins with participants, provide incentives to encourage continued engagement, and monitor environmental conditions closely to assess their impact on the project. By anticipating these challenges, we aim to minimize their potential effects on the study's results.

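### The protocol states two incompatible follow-up schedules, one ending at 12 months and one at 5 years, with no common time zero

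*Protocol article*

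**What the plan says.** **Long schedule.** Section 3.8 reads "Participants will be assessed at baseline, 1 year, 3 years, and 5 years after the intervention starts". The same section has nutritional, socioeconomic and health status measured at every one of these visits.

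**Short schedule.** The abstract reads "Data collection will occur at three intervals: baseline, 6 months, and 12 months post-intervention". Section 3.10 gives "baseline, 6 months, and 12 months post-intervention" as the example for the mixed-effects models and uses baseline to 6 months as the example for the paired tests. Section 4.3 expects "difficulties in retaining participants for follow-up assessments over the twelve-month study period".

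**Number of visits.** Section 3.9, directly after 3.8, reads "Primary and secondary outcome measures will be assessed in three-time points".

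**Intervention period.** Section 4.2 says of planting and workshops, which run concurrently, that "these activities span in total 5 years". Section 4.2.1 says of planting: "Spanning ~9 months, this activity not only focuses on the technical aspects of reforestation". Section 4.2.2 describes the workshops as "Scheduled over 10 months".

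**Linked provisions.** Section 3.4 raises the required 276 families to 300 per commune because attrition is expected. Section 3.1 promises the control commune the food forest once the study period is over, subject to funding. Section 3.11 makes it available as soon as there is funding.

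**The concern.** The visit schedule is a basic design element, and the article gives two versions of it as current text. A field team following 3.8 would not visit at 6 months and would return at 3 and 5 years. A team following the abstract would do the opposite.

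Three things depend on the answer:

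- **What the outcome data measure.** An early visit may fall while the intervention is still being delivered.
- **Whether the attrition allowance is adequate.** The same allowance has to cover one year of loss or five.
- **Whether a control group still exists at the later visits.** If the study period is twelve months, the delayed intervention could reach the control commune before years 3 and 5, and the randomised contrast at those visits would be lost.

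**Working it through.** **1. The two visit sets, in months**

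| Source | Visits | Number | Clock |
|---|---|---|---|
| Abstract; examples in 3.10 | 0, 6, 12 | 3 | post-intervention, not defined |
| 4.3 | study period of 12 | not given | not given |
| 3.8 | 0, 12, 36, 60 | 4 (3 after baseline) | from the start of the intervention |
| 3.9 | not given | 3 | not given |

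The common visits are 0 and 12. Months 6, 36 and 60 each appear in one schedule only. The last follow-up is at 12 or 60 months, a difference of 48 months and a ratio of 60/12 = 5.

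Section 3.9 does not decide between them. Its count of three fits baseline, 6 and 12 months. It also fits the three post-baseline visits of 3.8.

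**2. Where the 6-month visit falls**

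The inputs are planting of about 9 months (4.2.1) and workshops of 10 months (4.2.2). Both are assumed to begin at the start of the intervention, since 4.2 has them run concurrently.

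- Counted from the start, month 6 is 9 − 6 = 3 months before planting ends and 10 − 6 = 4 months before the workshops end. If delivery is even over time, 6/9 = 67% of the planting period and 6/10 = 60% of the workshop period have passed.
- Counted from the start, month 12 is 12 − 9 = 3 months after planting ends and 12 − 10 = 2 months after the workshops end.
- Counted from the end of planting, the visits fall at 9 + 6 = 15 and 9 + 12 = 21 months after the start.

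Only the count from the start fits the twelve-month study period in 4.3.

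**3. The attrition allowance**

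The plan's own figures come first. n₀ = 1.96² × 0.5 × 0.5 / 0.05² = 384.16, stated as 384. With the finite population correction, 384.16 / (1 + 383.16/968) = 275.2, rounded up to 276. Both stated figures reproduce.

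The loss that 300 can absorb is 1 − 276/300 = 0.08, or 8% in total over the whole follow-up. The article gives no loss rate, so the rates below are assumptions.

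| Assumed total loss | Families left of 300 | Families needed to keep 276 |
|---|---|---|
| 8% | 276 | 276/0.92 = 300 |
| 10% | 270 | 276/0.90 → 307 |
| 20% | 240 | 276/0.80 = 345 |
| 30% | 210 | 276/0.70 → 395 |

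An 8% total loss is a different requirement over 12 months than over 60, and the article does not say which period it covers.

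**4. The control condition**

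Sections 3.1 and 4.3 read together release the control commune after month 12, if funds are available. Section 3.8 then has two further visits, at months 36 and 60. Section 3.11 ties the release to funding alone. No section says that the control commune stays untreated until the last comparative visit.

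**The case against.** Several points on the other side are sound.

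- **The visits in 3.10 are examples.** They are marked as such, month 12 is the same as year 1, and a mixed-effects model can take any visit set. So the models in 3.10 are not shown to be wrong. Only their time points need to be aligned. The abstract and 4.3, however, state the short schedule without that qualifier.
- **Three against four time points is not a separate contradiction.** The wording in 3.9 is ambiguous and adds little to the main conflict.
- **The planting point is conditional.** The 6-month visit appears only where the clock is called post-intervention, and the clock from the start appears only in 3.8, which has no 6-month visit. If the count ran from the end of planting, the 6-month visit would come after it. The undefined clock is itself part of the problem.
- **A named primary visit can sit in a statistical analysis plan.** Its absence from the article is not a fault by itself. But an analysis plan cannot choose from a visit list that the protocol contradicts.

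A reader might also infer more than the text supports:

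- *A false-positive rate of about 19% from testing four follow-up visits.* That count pools two schedules that cannot both apply, and it treats repeated measures on the same families as independent.
- *A 12-month visit in year 6, counted from the end of the 5-year activities.* The twelve-month study period in 4.3 excludes this.
- *That an early visit must not carry an effectiveness test.* This is a preference. A repeated-measures model may include an early visit, and by month 6 a good part of both activities may have been delivered.
- *That too little time has passed at month 12 for any yield.* The article gives a harvest interval of 3 months but no date for the first harvest.

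**Conclusion.** The contradiction stands on the current text and needs no assumption. Section 3.8 and the short schedule in the abstract and 4.3 cannot both be the follow-up plan. They share baseline and month 12 and differ by 48 months in length. This is an internal inconsistency, not detail left to another document, and it must be settled because it determines which data are collected.

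Three consequences rest on stated conditions:

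- The 6-month visit precedes the end of planting by about 3 months and the end of the workshops by 4, provided that visits and both activities count from the start.
- The allowance covers 8% total loss relative to the plan's own target of 276. Whether that is enough depends on the follow-up length and on a loss rate that the article does not give.
- The comparison at years 3 and 5 is at risk if the study period is twelve months and funding for the delayed intervention arrives before those visits. The article does not say that this will happen, but nothing in it prevents it.

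**What to change.** 1. Reconcile the abstract, 3.8, 3.9, 3.10 and 4.3 to one list of visits with one defined time zero. State in 3.9 whether the count includes baseline.
2. Align the examples and the repeated-measures time points in 3.10 with that list.
3. State which retained visit carries the primary comparison, chosen with regard to the plan's own planting and workshop periods. Interpret any visit before those periods end as an early result under partial exposure.
4. If the 3- and 5-year visits are kept, reconcile 3.1 and 3.11 with them. State either that the delayed intervention in the control commune follows the last comparative visit, or that the later visits are not controlled comparisons.
5. State the follow-up length and loss rate that the increase from 276 to 300 is meant to cover.

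If the choice is made before visits begin, the document change is wording only. The choice itself is not free: the longer schedule means four more years of fieldwork and retention, and possibly more families per commune. The shorter one gives up the long-term outcome data.

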### 3.9 Measurements

Primary and secondary outcome measures will be assessed in three-time points.

The primary and secondary outcomes of this study are centered around assessing the nutritional, socioeconomic, and health statuses of the participants.

#### 3.9.1 Primary outcome

Nutritional Status—The focus is on evaluating participants' nutritional health through a detailed questionnaire designed to provide both quantitative and qualitative insights into their dietary habits and the quality of their nutrition.

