### 2.2 Specific objectives

To determine the effect of the Food Forest initiative on dietary diversity, malnutrition rates, and overall nutritional status of participating communities.To analyze changes in household income levels, employment opportunities, and economic stability as a result of the Food Forest activities.To examine the influence of the Food Forest initiative on physical and mental health, including general health perception, physical functionality, and emotional wellbeing among participants.

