To align with the nature of the data, nutritional and health status variables will be analyzed at the individual level, allowing us to capture specific health outcomes for each family member. Socioeconomic variables, including food security (measured by the Household Food Insecurity Access Scale [HFIAS]) and dietary diversity, will be evaluated at the family level. This approach enables a comprehensive analysis by distinguishing between individual health measures and collective socioeconomic conditions.

For older adult participants, the *Mini Nutritional Assessment (MNA)* will be used to assess undernutrition risk. For all other participants, individual nutritional status will be determined through anthropometric measurements (weight, height, and age). Household-level dietary diversity will be measured with a dietary diversity questionnaire, enabling us to capture a broader picture of household nutritional intake.

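### The primary outcome, nutritional status, is defined inconsistently across sections, and no single primary result is identified

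*Protocol article*

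**What the plan says.** Section 3.9.1 names one primary outcome, nutritional status, assessed "through a detailed questionnaire designed to provide both quantitative and qualitative insights into their dietary habits and the quality of their nutrition". It gives no variable, population, visit or summary measure.

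The measurement and analysis sections describe three different things:

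- **MNA.** Section 3.5.1 states "This study will incorporate 14 specific questions from the MNA", and then "this tool will be used only with older adult participants in our sample".
- **Anthropometry.** For other age groups, section 3.5.1 says "nutritional status will be assessed using anthropometric measurements, including weight, height, and age, to calculate Body Mass Index (BMI) and other relevant indicators". Section 3.10 repeats this split by age.
- **Household diet.** Section 3.5.1 adds a modified dietary diversity questionnaire at family level.

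In section 3.10, the paragraph on group comparisons gives BMI and dietary diversity scores as its examples of nutritional status. The regression paragraph says "linear regression will be used to assess continuous outcomes such as household income levels, nutritional status (BMI), or dietary diversity scores". Later the same section says "Socioeconomic variables, including food security (measured by the Household Food Insecurity Access Scale [HFIAS]) and dietary diversity, will be evaluated at the family level", while nutritional variables are to be analysed per individual. All tests are two-tailed at p < 0.05, and no order or adjustment is given.

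The first specific objective in section 2.2 covers "dietary diversity, malnutrition rates, and overall nutritional status of participating communities".

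**The concern.** The primary outcome is the result on which a trial is judged, so a reader must be able to say in advance which number that is. Here the definition in 3.9.1 and the measurements in 3.5.1 and 3.10 do not describe the same thing. The one named nutrition questionnaire for individuals is restricted to older adults. Weight and height are not a questionnaire and do not measure dietary habits. The remaining questionnaire, on dietary diversity, is nutritional in some sentences and socioeconomic in another.

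With a common threshold of 0.05 and no deciding variable, a favourable MNA, BMI or dietary diversity result could each be presented as the primary finding once the data are seen. There is also a difficulty of interpretation. BMI is the only anthropometric variable that the analysis section names, and it is treated there as continuous. A higher mean BMI could be a benefit where undernutrition dominates, or a harm where the ultra-processed diets described in the introduction dominate. The direction that would count as success is not stated.

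**Working it through.** **1. The plan's own figure.** Inputs from section 3.4: Z = 1.96, p = 0.5, E = 0.05, N = 968 families.

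- n0 = Z² p(1 − p)/E² = 3.8416 × 0.25/0.0025 = 384.2, against about 384 stated.
- With the finite population correction: n0/(1 + (n0 − 1)/N) = 384.16/(1 + 383.16/968) = 275.2, rounded up to 276 as stated.
- 300 per commune leaves 24/300 = 8% for attrition.

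The figure reproduces. It is a precision calculation for one proportion of 0.5 and refers to none of the nutrition measures, so it does not reveal which variable was meant as primary.

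**2. The sections side by side.**

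| Measure | Who or what is measured | Questionnaire on diet, as in 3.9.1? | Class in the protocol |
|---|---|---|---|
| 14 MNA items | older adults | partly | nutritional |
| BMI and unnamed other indicators | all other ages | no | nutritional |
| Dietary diversity | household | yes | nutritional in 2.2, 3.5.1 and part of 3.10; among socioeconomic variables elsewhere in 3.10 |

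No row meets 3.9.1, covers all participants and is classed consistently. Section 3.4 adds a further mismatch: the head of household reports on the family's nutritional situation, whereas 3.10 analyses nutritional status per person.

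**3. Error rate if any of the measures may decide.** With k independent tests at 0.05, the chance of at least one false positive is 1 − 0.95^k.

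- k = 2 (BMI and dietary diversity, the two that 3.10 names in its tests): 1 − 0.9025 = 9.75%.
- k = 3 (adding the MNA): 1 − 0.857375 = 14.3%.

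The documents give no correlations, so a range was assumed and simulated (400,000 multivariate normal draws, equal pairwise correlation, two-sided 0.05):

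| Correlation | 2 tests | 3 tests |
|---|---|---|
| 0.3 | 9.5% | 13.6% |
| 0.5 | 9.1% | 12.4% |
| 0.8 | 7.8% | 9.8% |

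These figures are for one visit. Repeated visits are not counted, because section 3.10 also plans mixed models across time and the number of follow-up visits is itself in conflict. The figures cover multiplicity alone and ignore clustering by commune.

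**4. Visits.** The abstract and section 3.10 give baseline, 6 and 12 months. Section 3.8 gives baseline, 1, 3 and 5 years. Section 3.9 speaks of three time points. A primary visit cannot be read from the text.

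**The case against.** The best defence is that this is a condensed article. Cut-offs, anthropometric indices and test details are usually left to the analysis plan, and 3.10 introduces many of its variables only as examples. It also separates individual from family measures, so it never proposes to merge the three into one score. The sentence placing dietary diversity among socioeconomic variables mainly sets the level of analysis. Section 3.9.2 defines the secondary socioeconomic outcome as five strata and does not list dietary diversity.

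Much of this stands, and it limits what can be claimed:

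- A reader might infer that unstandardised BMI is used for everyone who is not an older adult. Section 3.10 suggests this by naming only BMI, but 3.5.1 also records age and allows other indicators, so it is implied and not stated. Even if raw BMI were used in children, both groups age over the same interval. Growth would mainly add noise to the between-group contrast, and would distort chiefly the within-group paired tests.
- A reader might infer that opposite BMI changes will cancel. The documents give no distribution of under- or overweight, so this is only a possibility.
- A reader might infer that no malnutrition category will be analysed. Section 3.10 provides methods for categorical outcomes but names no such category among its examples.
- A reader might count all secondary outcomes and visits and reach far higher error rates. Those outcomes are not enumerated, are not independent and do not bear on the primary claim.
- A reader might put a margin of error on the MNA result. That would need the share of older adults, which the documents do not give.

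The defence does not reach the core. The identity of the primary variable belongs in the protocol. Here the protocol does speak to it, and its statements disagree. An analysis plan could settle the matter only by overriding one of them.

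**Conclusion.** The point holds as a contradiction in what the protocol states. Nutritional status is a diet questionnaire in 3.9.1, three measures in different people and units in 3.5.1 and 3.10, and includes or excludes dietary diversity depending on the sentence. Nothing says which result decides.

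If all three may decide at one visit, the false-positive rate is about 14% under independence and about 10% to 14% at assumed correlations of 0.8 to 0.3, against a nominal 5%. Section 3.10 names no specific test for the MNA. With BMI and dietary diversity alone, the rate is about 8% to 10%.

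A reader might go further and infer that the trial can have no valid primary result. The text does not support that. What is missing is a single identified result, and naming one repairs this defect. The documents give no effect size, standard deviation or power for any nutrition variable, so power after the change cannot be computed.

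**What to change.** Before any outcome data are analysed:

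1. Name one primary variable, its population, one visit and one between-group contrast in 3.9.1, and use the same wording in 3.5.1 and 3.10. The household dietary diversity score is a natural candidate: it is already planned, covers every sampled family and fits the dietary-habits wording of 3.9.1. The choice remains the investigators'.
2. Reconcile the visit schedules (6 and 12 months against 1, 3 and 5 years) so that the primary visit exists. The contrast must also say whether the control is one commune (abstract, 3.1) or two (3.3).
3. Class dietary diversity once, and correct the sentence in 3.10 if it is to be nutritional.
4. Make the other nutrition measures secondary, reserve the p < 0.05 claim for the primary, and report the rest as estimates with intervals. If all three are to stay primary, a Bonferroni split gives 0.05/3 = 0.0167 each.
5. State that children's anthropometry is analysed as age- and sex-standardised z-scores, and adults' BMI also by under-, normal and overweight category. This defines the direction of benefit and answers the malnutrition-rates objective.

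The cost is protocol and analysis wording, since the measurements are already planned. The downside is that fewer outcomes can be called significant.
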